## Abstract

**Background:**

Chronic heart failure has high morbidity and mortality, with approximately half of the patients dying within 5 years of diagnosis. Recent additions to the armamentarium of anti–heart failure therapies include angiotensin receptor-neprilysin inhibitors (ARNIs) and sodium/glucose cotransporter 2 inhibitors (SGLT2is). Both classes have demonstrated mortality and morbidity benefits. Although these new therapies have morbidity and mortality benefits, it is not known whether rapid initiation is beneficial when compared with the conventional, slower-stepped approach. Many clinicians have been taught that starting with low-dose therapies and gradually increasing the dose is a safe way of intensifying treatment regimens. Pharmacologically, it is rational to use a combination of drugs that target multiple pathological mechanisms, as there is potential synergism and better therapeutic outcomes. Theoretically, the quicker the right combinations are used, the more likely the beneficial effects will be experienced. However, rapid up-titration must be balanced with patient safety and tolerability.

**Objective:**

This study aims to determine if early addition of ARNIs, SGLT2is, β-blockers, and mineralocorticoid receptor antagonists (within 4 weeks), when compared with the same therapies initiated slower (within 6 months), will reduce all-cause mortality and hospitalizations for heart failure in patients with stable heart failure with reduced ejection fraction.

**Methods:**

This is a single-center, randomized controlled, double-arm, assessor-blinded, active control, and pragmatic clinical trial. Adults with stable heart failure with reduced ejection fraction and idiopathic dilated cardiomyopathy will be randomized to conventional sequencing (the control arm; over 6 months) of anti–heart failure therapies, and a second arm will receive rapid sequencing (over 4 weeks). Study participants will be followed for 5 years to assess the safety, efficacy, and tolerability of the 2 types of sequencing. Posttrial access and care will be provided to all study participants throughout their lifespan.

**Results:**

We are currently in the process of obtaining ethical clearance and funding.

**Conclusions:**

We envisage that this study will help support evidence-based medicine and inform clinical practice guidelines on the optimal rate of sequencing of anti–heart failure therapies. A third placebo arm was considered, but costs would be too much and not providing study participants with therapies with known morbidity and mortality benefits may be unethical, in our opinion. Given the post–COVID-19 economic downturn and posttrial access to interventions, a major challenge will be acquiring funding for this study.

**International Registered Report Identifier (IRRID):**

PRR1-10.2196/44027

## Introduction

### Background

The current management of heart failure with reduced ejection fraction (HFrEF) has been revolutionized by the emergence of novel classes of drugs, namely, angiotensin receptor-neprilysin inhibitors (ARNIs) and sodium/glucose cotransporter 2 inhibitors (SGLT2is) [1,2]. With landmark clinical trials [3-6] demonstrating the efficacy of the latter drugs, there has been a paradigm shift in initiating and sequencing optimal anti–heart failure therapy and a concomitant reevaluation of the evidence base that guides conventional heart failure management. The American Heart Association heart failure guideline supports the rapid titration of guideline-based therapies every 1-2 weeks, with the goal of achieving target doses [7]. However, the European Society of Cardiology does not contain a timeline for the initiation of guideline-based heart failure therapy [8]. Pharmacologically, it is rational to use a combination of drugs that target multiple pathological mechanisms, as there is potential synergism and better therapeutic outcomes. Theoretically, the quicker the right combinations are used, the more likely the beneficial effects will be experienced. However, rapid up-titration must be balanced with patient safety and tolerability.

Sacubitril and valsartan, β-blockers, mineralocorticoid receptor antagonists (MRAs), and SGLT2is are disease-modifying agents that are used as combination therapy and are now regarded as a foundational therapy for HFrEF [1,2]. The conventional approach to initiating and optimizing HFrEF therapy reflects the sequence in which drugs were developed and trialed over the past 40 years [1]. Clinicians initiate therapy with an angiotensin-converting enzyme inhibitor or angiotensin receptor blocker, followed by a β-blocker, then an MRA, then a neprilysin inhibitor, and, finally, an SGLT2i. Each drug required up-titration to the target dose, or the maximally tolerated dose, before initiating another class of drug, with a treatment period usually spanning >6 months [1].

This approach is limited by several clinical misconceptions and assumptions: first, the most efficacious anti–heart failure therapies were developed first. The counterargument is exemplified by the fact that digitalis has been used in clinical practice for 200 years, yet it is no longer considered a key therapeutic agent. Second, drug efficacy is only achieved at maximum target doses [1]. However, studies have demonstrated morbidity and mortality reduction with the use of low-dose anti–heart failure therapy in HFrEF, with maximum target doses adding only a smaller clinical benefit. Third, the efficacy and safety of individual anti–heart failure drug class were assessed in clinical trials that required patients to be receiving all background therapy at target doses. However, most trials were conducted with patients receiving subtarget doses of anti–heart failure therapy [2].

Initiating drugs over a 6-month period is undesirable for several reasons. Practically, target doses of anti–heart failure therapy are infrequently achieved due to patient factors (nonadherence, perceived adverse effects, and costs), drug factors (adverse effects and frequency of dosing), physician factors (clinical inertia and limited time), inadequate patient follow-up, and a lack of perceived benefit of higher drug doses. Furthermore, there is a strong evidence base suggesting that the use of each of the foundation drugs has demonstrated morbidity and mortality reduction within 30 days of therapy initiation [1,2,9].

The aim of this study is to determine if early addition of ARNIs, SGLT2is, β-blockers, and MRAs (within 4 weeks), when compared with the same therapies initiated slower (within 6 months), will reduce all-cause mortality and hospitalizations for heart failure in patients with stable HFrEF.

### Rationale

The use of ARNIs and SGLT2is in low- to middle-income country settings is limited by high cost and accessibility. Despite the strong body of evidence supporting the safety and efficacy of ARNIs and SGLT2is, these agents are not yet included in the South African Essential Drug List. ARNIs and SGLT2is are available to private funders, yet access is limited as costs are only partially reimbursed by medical insurance schemes. Furthermore, SGLT2is have not yet been approved for heart failure by the South African Health Products Regulatory Authority, and use within clinical practice is predominantly off-label. Donations by the pharmaceutical industry have enabled limited access to ARNIs and SGLT2is in the public sector.

The challenge in this regard is maximizing access and rationalizing the use of ARNIs and SGLT2is while canvassing for widespread cost-effective rollout in the public sector.

The data on ARNIs and SGLT2is from high-income country settings suggest that morbidity and mortality reduction is achieved early in the clinical presentation of heart failure [1,2]. There, however, remains a paucity of data on the safety and efficacy of these drugs in sub-Saharan Africa.

Within sub-Saharan Africa, the main driver of heart failure remains hypertension, with ischemic heart disease emerging as a key etiology. There, however, is a growing cohort of young patients with idiopathic dilated cardiomyopathy with HFrEF who are often suboptimally medically treated with minimum prospects of receiving heart transplants. In our opinion, such a group of patients would ideally benefit from ARNIs and SGLT2is. Data from key clinical trials have demonstrated the use of ARNIs as de novo therapy in patients presenting with heart failure [3,10,11]. The latter trials have argued against the use of angiotensin-converting enzyme inhibitors or angiotensin receptor blockers upfront with a transition phase to ARNI therapy, as there would be merely a delay in using the most effective therapy with a concomitant risk of sudden cardiac death.

The rapid initiation of anti–heart failure therapy described above seems rational in a high-income country setting where drug monitoring and assessment of adverse reactions are facilitated by the ease and rapidity of access to health care facilities [1,2]. However, in low- to middle-income country settings, the infrequent and irregular access to health care facilities limits instituting the rapid initiation algorithm for heart failure therapy. Furthermore, there is a lack of robust data and randomized controlled trials comparing rapid initiation versus a slower, phased initiation of heart failure therapy [1].

### Study Objectives

#### Primary Objective

The primary efficacy end point is the composite end point of all-cause mortality and hospitalization for heart failure.

#### Secondary Objectives

Secondary end points include death from cardiovascular causes (eg, cardiogenic shock, myocardial infarction, tachycardia, or brady-arrythmia), improvement in the 6-minute walk test, improvement in the New York Heart Association functional class, improvement in symptoms as per the Kansas City Cardiomyopathy Questionnaire, trans-esophageal echo-determined ejection fraction (chamber dilatation, left ventricular systolic function, global longitudinal strain, and speckle tracking), and N-terminal prohormone of brain natriuretic peptide levels. Adverse drug reactions will also be collected and analyzed.

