## Methods

### Proposed Novel and Rapid Sequencing

The proposed algorithm for initiation of anti–heart failure therapy comprises of 3 steps once clinical euvolemia has been achieved with diuresis [2].

Step 1 is the concurrent initiation of treatment with a β-blocker and an SGLT2i. β-Blockers are pertinent in the treatment of HFrEF, especially in the context of reducing sudden cardiac death. Evidence has demonstrated reduced hospitalization for heart failure with the use of SGLT2is. The early diuretic effect of SGLT2is may attenuate the early risk of worsening heart failure when β-blockers are initiated [2].

Step 2 comprises of the addition of an ARNI (sacubitril and valsartan) within 1-2 weeks of step 1. The presence of hypotension (systolic blood pressure <100 mm Hg) warrants evaluation of blood response with an angiotensin receptor blocker before switching to an ARNI [2].

Step 3 is the addition of an MRA, within 1-2 weeks of step 2, depending on the serum potassium and the presence and degree of renal impairment. ARNIs and SGLT2i may improve renal function and potassium homeostasis, thereby permitting the use of MRAs. In patients with hypotension, MRAs may be used as step 2 [2].

The above algorithm represents a generic approach and may be individualized to specific scenarios. Patients with decompensated heart failure are a subgroup that require greater caution when initiating anti–heart failure therapy. β-Blocker therapy should only be initiated in the hospital after discontinuation of intravenous therapy for several days and the patient is clinically euvolemic, defined as the absence of rales and ascites and the presence of minimal peripheral edema [2].

In the appropriate patient, treatment with all 4 foundational treatments may be achieved within 4 weeks, with subsequent dose up-titration. This strategy increases the probability that highly effective therapies will be implemented in a manner that reduces mortality and hospitalizations and enhances the tolerability of subsequently administered treatments [1]. Figure 1 shows the proposed study flow diagram, which contains the novel and conventional sequencing approaches. A key difference is the rate at which therapies are added, with the novel sequence arm having patients on all the efficacious therapies initiated within 4 weeks.

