#### Study Design

This is a prospective, double-arm, randomized, assessor-blinded, and pragmatic clinical trial. The study will take place at a single site, that is, Tygerberg Hospital, Western Cape, South Africa.

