## Discussion

### Principal Findings

This study aims to determine if rapid sequencing of anti–heart failure drugs with proven morbidity and mortality benefits would be superior to slower titration of these therapies.

We chose a composite end point to reduce the sample size, as a larger sample size would result in greater costs and reduce the feasibility of the study. Given the high mortality and frequent hospitalizations for heart failure, we included both events in the combined primary efficacy endpoint.

Intuitively, it makes sense to ensure that the most efficacious heart failure therapies are initiated as soon as possible. Given that the therapies have varied modes of action, we hypothesize that if they are started together as soon as possible, they would have greater benefits than starting them later. Combination therapies are likely to target different pathophysiological aspects of heart failure and thus improve clinical outcomes. Issues with rapid initiation may potentially include hypotension and other adverse effects. We will guard against hypotensive events by starting with the lowest possible dose and stopping the drug if the patient becomes hemodynamically unstable. Furthermore, study participants are required to be euvolemic before rapid sequencing so that we do not worsen patients’ heart failure and thus limit hemodynamic instability and decompensated heart failure. It is a standard clinical practice to ensure euvolemia before titration of anti–heart failure therapies. Euvolemia is usually achieved by loop diuretics [8].

We chose a relatively young group of patients so that underlying issues such as ischemic heart disease are less probable and would not serve as confounders. Furthermore, this group of patients may benefit from the increased life expectancy as compared with the older group.

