### Limitations

The study is proposed to use one study site in the Western Cape of South Africa, which may not be reflective of the demographics of the South African population. Due to the nature of the study and means of intervention, implementation of a placebo-controlled arm will not be possible but is nonetheless cited as a limitation.

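### The only safety measure named is the adverse drug reaction, which depends on attribution to a drug in a trial whose treatment pace is unmasked

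*Protocol article*

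**What the plan says.** The Abstract (Methods) sets the aim: "Study participants will be followed for 5 years to assess the safety, efficacy, and tolerability of the 2 types of sequencing". The Discussion (Principal Findings) repeats that safety and tolerability data will be collected. Both the Abstract and the Introduction present safety and tolerability as what rapid up-titration has to be weighed against.

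The measure is named in one sentence of Secondary Objectives: "Adverse drug reactions will also be collected and analyzed". Adverse drug reactions appear once more, as a withdrawal criterion in Textbox 1. Table 1 gives a row to every other secondary end point in that section, but none to safety or tolerability. The Discussion does name the harm it expects, "Issues with rapid initiation may potentially include hypotension and other adverse effects", but hypotension is not made an outcome.

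On masking, Study Design says: "This is a prospective, double-arm, randomized, assessor-blinded, and pragmatic clinical trial". No arm receives placebo; the Limitations section says that "implementation of a placebo-controlled arm will not be possible but is nonetheless cited as a limitation". The arms differ visibly in pace. Proposed Novel and Rapid Sequencing says: "A key difference is the rate at which therapies are added, with the novel sequence arm having patients on all the efficacious therapies initiated within" a period given as 4 weeks; the control arm takes 6 months. The Discussion adds that a separate person will collect and analyze the data, and that clinicians will not be asked for work beyond their usual clinic duties.

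**The concern.** An adverse event is something that happened. An adverse drug reaction is an event that someone has judged to be caused by a drug. By naming the reaction, the article makes the safety comparison depend on that judgment. The intervention is the speed at which drugs are added, and anyone treating the patient can see it. If events are recognized or attributed differently by arm, the reaction rates will differ even when the true event rates do not, or a true difference may be hidden.

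What is at stake is the second half of the trial's question. A benefit on the primary composite would support rapid sequencing only alongside a credible statement that it is acceptably safe and tolerated. Because reactions are also a withdrawal criterion, differential attribution could affect withdrawals too.

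**Working it through.** The plan gives no figure for safety, so there is none to reproduce. The check is a reading of the text, followed by an illustration of size.

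**Step 1. Aim against measure**

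| Aim | Measure named | Table 1 row |
|---|---|---|
| Efficacy | Composite and its components; cardiovascular death, walk test, NYHA class, KCCQ, echocardiography, natriuretic peptide | Yes |
| Safety | Adverse drug reactions | None |
| Tolerability | None beyond adverse drug reactions | None |

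**Step 2. Where arm knowledge can enter**

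An event becomes a counted reaction in four stages.

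1. Recognized: the article names no one. Clinicians do their usual work and can see the pace of treatment.
2. Recorded: the same.
3. Attributed to a drug: no one is named and blinding is not stated.
4. Collected and analyzed: a separate individual, whose blinding is not stated. The trial is called assessor-blinded, but the article does not say which assessments this covers.

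Blinding stage 4, or stages 3 and 4, cannot recover events lost at stages 1 and 2. Counting events regardless of attribution removes stage 3. Values measured over common windows reduce the dependence on stages 1 and 2.

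**Step 3. Possible size (assumed rates)**

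The only input from the document is 292 patients per arm (Sample Size). The true risks and capture rates below are assumptions. Capture is the probability that an event ends up as a counted reaction.

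Recorded risk = true risk × capture. With equal true risk, the apparent ratio is capture₁ / capture₀, whatever the true risk.

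Take a true risk of 15% in both arms (0.15 × 292 = 43.8, about 44 patients each):

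- Capture 90% and 60%: 0.15 × 0.90 = 13.5%; 0.15 × 0.60 = 9.0%; ratio 1.5.
- Capture 80% and 70%: 0.15 × 0.80 = 12.0%; 0.15 × 0.70 = 10.5%; ratio 1.14.

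If the arm with better capture is reversed, the ratios are 60/90 = 0.67 and 70/80 = 0.88.

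The chance of a falsely significant difference (two-sided 0.05) is about Φ[(|p₁ − p₀| − 1.96 × SE₀) / SE₁], with SE₀ = √(2p̄(1 − p̄)/292) and SE₁ = √((p₁(1 − p₁) + p₀(1 − p₀))/292). With a true risk of 20% in both arms and capture of 50% in the control arm:

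| Capture, rapid arm | p₁ | p₀ | Ratio | Chance of false significance |
|---|---|---|---|---|
| 60% | 0.12 | 0.10 | 1.2 | 12% |
| 70% | 0.14 | 0.10 | 1.4 | 32% |
| 80% | 0.16 | 0.10 | 1.6 | 58% |

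At a true risk of 30% the last column becomes 16%, 47% and 79%. These figures show only what differential capture would do. They do not show that this trial has it.

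**The case against.** The strongest reply is that this is a condensed article. Event definitions, causality procedures, laboratory schedules and safety tables normally sit in the full protocol or analysis plan, so their absence here is no error. That stands for the procedures. It does not dispose of the point, because the article is not silent: it chooses the reaction as its unit, and the choice can be judged as stated.

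Several stronger readings are tempting and are not supported:

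- **That an unblinded treating clinician makes the attribution.** No sentence says so. The trial is called assessor-blinded and a separate person collects the data, so blinded causality assessment is neither confirmed nor excluded.
- **That the rapid arm is watched more closely.** A reader might infer this from the third step of the rapid sequence, where the mineralocorticoid receptor antagonist is added "depending on the serum potassium and the presence and degree of renal impairment". But the Discussion says both groups receive the same therapies, and nothing confines these checks to one arm. The text gives no visit schedule, and Figure 1 was not available for this check.
- **That the investigators will under-attribute.** The Discussion does expect few problems, but in answer to doubts about running a trial in a resource-limited setting. It is not evidence of bias.
- **That nothing free of attribution is measured.** All-cause mortality and heart failure hospitalization need no drug attribution and would capture the gravest harms. They are labelled efficacy, however, and do not count hypotension, hyperkalemia or renal worsening that falls short of them.

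It is also fair to say that comparing measured values at only two fixed visits would miss transient events. The fix therefore uses time windows.

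**Conclusion.** The point holds in limited form. The article promises a comparison of safety and tolerability, names only an attribution-dependent measure for it, and states nothing that makes recognition or attribution independent of arm while treatment pace is unmasked. Followed as written, this leaves the safety comparison open to bias.

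The size and direction are unknown, because the document gives neither an event rate nor a capture rate. The ratios of 1.14 to 1.5 are illustrations on assumed rates. The conclusion rests on two things: the ordinary meaning of an adverse drug reaction, and the absence of any stated safeguard at the recognition and attribution stages. If the full protocol already counts all adverse events, or has causality judged blind to arm, much of the point becomes a matter of wording.

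It should be corrected before the trial starts. It does not affect the primary end point.

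**What to change.** **Secondary Objectives.** Replace the sentence on adverse drug reactions with a comparison of adverse events between arms regardless of attribution. Keep drug reactions as a supplementary measure, with causality judged blind to arm, and say who makes that judgment.

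**Table 1, safety row.** Add an outcome built from measured blood pressure, potassium and renal function, with prespecified reporting thresholds. The eligibility cut-offs in Textbox 1 are one option: systolic pressure <100 mm Hg, potassium >5.4 mmol/L, estimated glomerular filtration rate <30 mL/min/1.73 m². They would serve as end point definitions only.

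**Table 1, tolerability row.** Add the proportion taking all four drug classes.

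**Timing.** Compare both rows over the same windows in both arms, for example to week 4 and to month 6, the stated lengths of the two sequences.

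**Cost.** There are more events to record. The control arm may need a value at a common time point that routine care would not have produced. Since the article promises clinicians no extra work, this should fall to the separate data collector. Funding and ethics approval are still pending, so the change is mainly one of wording now. No treatment rule changes.
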